For dyads living with dementia, several psychosocial intervention studies have demonstrated positive outcomes for both the caregivers and the people living with dementia. Dyadic interventions described in the research include a combination of psychoeducation, cognitive-behavioural therapy (CBT), and strategies for managing cognitive deficits and neuropsychiatric symptoms in dementia. The Acquiring New Skills While Enhancing Remaining Strengths program (ANSWERS) is a six-week strengths-based program comprising modules covering psychoeducation of dementia, communication skills, managing memory and strategies, physical activity, and recognising emotions and behaviours (Judge et al., 2010). The controlled trial reported that caregivers in the intervention group had improved mental health with reduced depressive and anxiety symptoms, less dyadic strain and role captivity, and improved mastery compared to controls [21]; however, outcomes for the individuals living with dementia have not been published. This face-to-face one-on-dyad intervention reported a high attrition rate (24%) in the intervention group, compared to 2% in the control group, with the authors hypothesising that the intervention may have been too time-consuming and overwhelming for the dyads [21].

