### 2.3. Participants and Recruitment

#### 2.3.1. Inclusion and Exclusion Criteria

Sixty dyads (sixty caregivers, sixty people living with YOD) living in Australia will be recruited. There is no restriction on the type of YOD. Participants will be recruited by advertising the study at the Royal Melbourne Hospital (such as the Neuropsychiatry YOD clinic), the Step-Up for Dementia Research Database, on social media, and through other forums such as Dementia Australia. Caregivers will be eligible to participate if they: (1) self-identify as a caregiver of a person living with YOD; (2) consider themselves in a long-term relationship with the person living with YOD (mostly will be spouses, but are not restricted); (3) score either ≥14 on the Depression subscale of the Depression Anxiety and Stress Scale, DASS-21 [38], ≥12 on the Anxiety subscale of the DASS, or ≥20 on the Stress subscale; (4) able to understand and communicate in English; (5) have functional hearing (with or without hearing aids or other devices); (6) have access to the internet and a device (laptop or tablet) at home; and (7) have an existing Facebook account or be willing to create one. Participants living with YOD will be eligible if they: (1) have a diagnosis of YOD (symptom onset <65 years); (2) have mild or moderate cognitive impairment, as measured by a Mini-Mental State Examination [39,40] score between 22–28); (3) able to tolerate approximately 100-min online sessions; (4) able to understand and communicate in English; (5) have functional hearing (with or without hearing aids or other devices); (6) have access to the internet and a device (laptop or tablet).

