#### 2.3.2. Procedure and Randomisation

Interested and potential dyads will receive a phone call whereby the above criteria will be discussed to check eligibility for entry. Following the screening, informed consent will be obtained by caregivers and people living with YOD. Dyads will be randomly allocated a computer-generated number 0 or 1. If they receive a “1”, they will be randomised into the intervention MAPS group. Each intervention group will have a maximum of seven dyads. For those dyads who receive a “0”, they will be allocated to the waitlist control group and be invited to participate in MAPS following the completion of the intervention. All eligible participants will be administered the outcomes measures (see below).

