### 2.5. Data Collection and Management and Statistical Analysis Plan

All self-report measures will be collected online using REDCaP and stored electronically. Dyads successfully screened into the program will be contacted and invited to an online session where the pre-program measures will be completed. Post-MAPS quantitative outcome measures will be collected by members of the research team who are masked to allocation. Post-MAPS qualitative evaluation will be audio-recorded and transcribed for analysis.

Our primary outcome measure is an improvement in the DASS-21 (pre- and post-), with a 4-point reduction (SD of differences = 8). Using β = 80% (power) and α = 0.05 and medium effect size = 0.5 (*p* < 0.05), we will require a sample size of n = 54 dyads. Accounting for 10% attrition, we aim to recruit 60 dyads. We thus anticipate approximately 9 “waves” of MAPS (i.e., 7 dyads per wave, accounting for at least one drop-out per wave). As the program involves sequential weekly sessions, we will not be able to replace drop-outs during the program. For demographic analysis, we will use frequencies and descriptive statistics. Categorical tests such as χ^2^ will be used to compare groups on factors such as dementia types and gender. Paired *t*-tests will be used to compare pre- and post- primary and secondary outcomes and we will also calculate effect sizes to determine the size of the changes in DASS-21 and other measures. Statistical Program for Social Sciences (SPSS) version 27 (IBM) will be used for quantitative analyses. Qualitative analysis of focus group interviews will use Interpretative Phenomenological Analysis to synthesise their experiences, benefits, and limitations of participating in the project.

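### The sample size allows for 10% attrition, but the wave plan in the same paragraph assumes at least 14%, so 54, 60 and nine waves of seven do not agree

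*Protocol article*

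**What the plan says.** Section 2.5 of the protocol article sets the sample size: "we will require a sample size of n = 54 dyads". It continues: "Accounting for 10% attrition, we aim to recruit 60 dyads". Section 2.3.1 repeats the target: "Sixty dyads (sixty caregivers, sixty people living with YOD) living in Australia will be recruited".

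Section 2.5 then turns this into delivery: "We thus anticipate approximately 9 “waves” of MAPS", explained in brackets as "7 dyads per wave, accounting for at least one drop-out per wave". Because the sessions are sequential, "we will not be able to replace drop-outs during the program". Section 2.3.2 sets the ceiling on group size: "Each intervention group will have a maximum of seven dyads".

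Three further statements bear on the point:

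- Section 2.1 gives 1:1 allocation and has the waitlist arm join MAPS only once its post-measures are complete.
- Section 2.5 names paired t-tests of pre against post scores as the analysis of the primary and secondary outcomes. It collects self-report measures online through REDCap.
- The Introduction describes an earlier dyadic program that "reported a high attrition rate (24%) in the intervention group, compared to 2% in the control group".

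**The concern.** Consecutive sentences put two different sizes on what reads as one quantity. The second is introduced as if it followed from the first. An allowance of 10% is fewer than one loss per wave of seven, so a plan that expects at least one per wave expects more than 10%.

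The recruitment target rests on the allowance. If the higher rate is the one the investigators believe, and if it means missing post scores, the 54 evaluable dyads are not secured by recruiting 60. A paired t-test needs both scores and so drops any dyad without a post score. Losses concentrated in the MAPS arm would also leave a selected group of completers in that arm. That would affect the validity of the comparison as well as its precision.

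**Working it through.** **Inputs.** From section 2.5: 54 required dyads, 10% attrition, 60 recruited, about nine waves, seven dyads per wave, at least one drop-out per wave, a 4-point change with SD 8 (standardised effect 4/8 = 0.5), alpha 0.05. From section 2.1: 1:1 allocation (30 per arm) and the waitlist timing. From section 2.3.2: the cap of seven.

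**1. The plan's own figure.** 54 / (1 − 0.10) = 60. This reproduces exactly, and the implied loss is 60 − 54 = 6 dyads.

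**2. The wave plan.** One of seven is 1/7 = 14.3%. Nine waves lose at least 9 × 1 = 9 dyads. Six losses over nine waves would be 6/9 = 0.67 per wave, below the stated minimum of one. Nine waves of seven is 63, and 63 − 9 = 54. Equivalently, 54 / (6/7) = 63. So the wave plan reaches 54 from 63 dyads, while the target is 60. Seven is the cap, so a smaller wave that loses one dyad has a rate above 14.3%.

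**3. Evaluable dyads if the per-wave rate applies to all 60 and costs the post score.** 60 × 6/7 = 51.4; counting by waves, 60 − 9 = 51.

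**4. Evaluable dyads if it costs post scores only in the randomised MAPS arm.** That arm fills 30/7 = 4.3 waves, so about four to five of the nine. Its evaluable number is 30 × 6/7 = 25.7, about 26. The article gives no separate waitlist loss before the post-measures, so I assume a range:

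| Assumed waitlist loss | Waitlist evaluable | Total evaluable |
|---|---|---|
| 0% | 30.0 | 55.7 |
| 10% | 27.0 | 52.7 |
| 14.3% | 25.7 | 51.4 |

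The total is therefore about 51 to 56, a range that contains 54.

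**5. Effect on power** (effect 0.5, alpha 0.05, t distribution; two-sided unless stated):

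| Test | Evaluable | Power |
|---|---|---|
| Paired, all dyads pooled | 54 | 95.0% |
| Paired, all dyads pooled | 51 | 93.8% |
| Between arms, SD 8 | 27 + 27 | 43.8% |
| Between arms, SD 8 | 25.7 + 25.7 | 42.0% |
| Paired, one-sided, one arm | 27 | 81.2% |
| Paired, one-sided, one arm | 26 | 79.8% |
| Paired, one-sided, one arm | 25 | 78.3% |

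The article does not state sidedness. The last three rows are included because 27 per arm, one-sided at 80% power, is one calculation that gives 2 × 27 = 54.

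**6. Illustration only.** With the cited program's losses, 30 × 0.76 = 22.8 MAPS dyads and 30 × 0.98 = 29.4 waitlist dyads would remain, 52.2 in total. Between-arm power at 23 against 29 is about 42%.

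**The case against.** The strongest reply is that the wave sentence is about session places. It sits beside the remark on replacing drop-outs and depends on a cap of seven. On that reading 60/7 = 8.6 gives approximately nine waves, and the plan of 9 × 7 − 9 does land on the required 54. This softens the point without removing it. One of seven exceeds 10% whatever the number of waves, and the route to 54 still starts from 63.

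A reader might infer that the trial will have 51 evaluable dyads and not 54. The documents do not support that as a flat statement. A waitlist dyad that leaves during its later MAPS wave has already given its post-measures, so that loss costs the trial comparison nothing. Nor does the article say that dyads who stop attending go unmeasured. The figure of 51 needs both a missing post score for every drop-out and a waitlist loss of about 14%.

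A reader might also project the 24% against 2% loss onto MAPS. That program was face-to-face and delivered to one dyad at a time, while MAPS is online and group-based, and the Introduction suggests that online delivery may ask for less time. The figures show that unequal loss is possible but do not predict it here.

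Finally, missing-data methods are commonly left to an analysis plan, which is not shown, so their absence is not a fault. The paired t-test is different: the article states it as the method, so what it does with missing post scores can fairly be raised.

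**Conclusion.** The inconsistency is real: 10% (six losses) against at least 14.3% (at least nine losses over nine waves), or 60 dyads against 63 for the same 54. Its consequence is modest. The evaluable total is about 51 to 56 and the randomised MAPS arm about 26 of 30. These figures assume equal arms of 30, exactly one loss per full wave, and a missing post score for each MAPS-arm drop-out; more than one loss per wave would lower them.

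Power moves by about one to two percentage points under a pooled paired test or a between-arm test. Only the one-sided reading with 27 per arm falls below 80%, and the article does not state that reading. The low between-arm power is a separate and larger matter that exists at 54 as well, and it should not be charged to attrition. The documents do not show that the trial must enrol 63 dyads, or that losses will bias the result. The point merits correction before the trial starts because the recruitment target is derived from this figure and the correction is cheap.

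**What to change.** 1. State one attrition rate, defined as the proportion of randomised dyads without a post DASS-21, and keep it apart from leaving the sessions.
2. Make 54, 60 and nine waves of seven agree by restating the evaluable number from 60 as a range and per arm (for example, about 26 of 30 in MAPS and about 51 to 56 overall, with the waitlist assumption given). No extra dyads are needed.
3. Say that about four to five of the nine waves form the randomised MAPS arm and that the rest serve the waitlist after its post-measures.
4. Seek the post DASS-21 through REDCap from every randomised dyad, including those who stop attending.
5. Compare the arms as randomised with a model that uses baseline and post scores, in place of completer-only paired t-tests. Add a sensitivity analysis in which MAPS drop-outs are assumed to do worse.
6. If the 24% against 2% pattern is used, label it an illustrative scenario.

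The cost is a few restated numbers, reminder messages and slightly more analysis. The Data Availability statement says the trial had not commenced, so nothing already collected is affected.

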## 2. Materials and Methods

### 2.1. Study Design

This pragmatic randomised waitlist control trial design with post-program focus groups will test the primary and secondary hypotheses with a 1:1 allocation ratio. People living with YOD and caregiver dyads will be randomised to one of two conditions: (1) MAPS; or (2) Waitlist control (Figure 1). Dyads randomised into the MAPS group will receive 8 × 100-min group sessions of combined psychotherapy and music therapy, supplemented with an optional online closed Facebook group with activities to be completed between sessions. Dyads will attend sessions 1 and 8 online together; however, from weeks 2 to 7, caregivers and people living with YOD will participate separately in online groups. Participants in the standard care group will participate in the MAPS program following completion of the post-measures. Data will be collected at baseline and the end of the 8-week intervention period. This trial is framed as a superiority trial where we hypothesise that the MAPS group will be superior to usual care for the primary outcome measure.

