### 2.4. Measures

Demographic information (age, gender), information about caregiving (duration and approximate hours per day), MMSE scores, treatments, and dementia type if known and severity (mild, moderate, severe pre- and post- program) will be collected. To detect changes in anxiety and depression in caregivers (primary outcome), the DASS-21 will be administered pre- and post-program. The DASS is a 21-item scale composed of three sub-scales with 7 items each, measuring depressive, anxiety, and stress symptoms, and has good psychometric properties (reliability and validity). Participants are asked to rate each item based on how they have been feeling the past week with a 0 (not at all) to 3 (most of the time) scale for responses. The score is multiplied by 2 to make scores equivalent to the DASS-42 [38].

Secondary outcome measures for the caregivers collected pre- and post-MAPS are:

Coping: The Brief COPE [41] is a 28-item questionnaire measuring three different types of coping, emotion-, problem- and avoidant-coping mechanisms, and has strong psychometric properties.

Revised Scale for Caregiving Self-Efficacy: [42] is a 15-item scale with 3 subscales that measure self-efficacy. It captures caregiver perspectives on respite, responding to disruptive behaviours, and controlling upsetting thoughts about caregiving. It has strong psychometric properties.

Social Connectedness: The Friendship Scale [43] is a 6-item scale measuring 6 dimensions that contribute to social isolation and social connection of older adults. Based on the last 4 weeks, participants rate each item on a 5-point Likert scale (0 = Almost always to 4 = Not at all) with total scores ranging from 0–24. Psychometric testing suggests good reliability (Cronbach’s α = 0.83) and sensitivity to change for known dimensions impacting social isolation.

Secondary outcome measures for the people living with YOD collected pre- and post-MAPS are:

Social Connectedness: The Friendship scale [43], as described above.

Mental health: The DASS-21 [38], as described above.

Behaviours using the Neuropsychiatric Inventory–brief form (NPI-Q) [44]. This brief version of the NPI-NH has 12 items measuring behaviours such as depression, hallucinations, and agitation/aggression. Caregivers are asked to rate the severity of how it affects the people with YOD (Mild, moderate, severe) and the distress the caregiver experiences (0 nil to 5 extreme distressing).

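### Outcomes are tested only by unadjusted paired t-tests and groups by baseline significance tests; a between-arm model adjusted for the baseline score would use data already collected

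*Protocol article*

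**What the plan says.** Section 2.5 of the protocol article fixes two sets of tests. After descriptive statistics for demographics, categorical tests, with χ² as the example, "will be used to compare groups on factors such as dementia types and gender". For outcomes, paired t-tests "will be used to compare pre- and post- primary and secondary outcomes", together with effect sizes. No other outcome test is named, and no covariate.

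Section 2.1 describes a randomised trial "with a 1:1 allocation ratio", framed as superiority of MAPS over usual care. In section 2.3.2, "Dyads will be randomly allocated a computer-generated number 0 or 1"; stratification is not mentioned. Section 2.4 lists what is known about each dyad before the program: age, gender, "information about caregiving (duration and approximate hours per day), MMSE scores, treatments, and dementia type if known and severity". For the primary outcome, "the DASS-21 will be administered pre- and post-program". The secondary measures for caregivers and for people with YOD are likewise collected before and after, so every outcome has its own baseline value.

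**The concern.** Two choices look wrong together.

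First, if allocation is random, any baseline difference between arms arose by chance, so a test of that difference addresses a null hypothesis known to be true. Whether an imbalance matters depends on its size and on how strongly the factor predicts the outcome. A p-value measures neither, and in a trial this small a sizeable gap will often be non-significant.

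Second, the stated outcome test cannot carry a covariate and has no arm term. The natural step from paired t-tests to a comparison of arms is to compare change scores. That leaves part of any chance difference in the starting score inside the estimated effect, and it is less precise than adjusting for the starting score. At stake is a shift that could be a sizeable fraction of the 4-point target, and precision forgone although the data to recover it are already collected.

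**Working it through.** **Inputs from section 2.5.** Target difference 4 points; SD of differences 8; α = 0.05 (sidedness not stated, two-sided used here); power 80%; 54 dyads, or 60 after 10% attrition. With 1:1 allocation that is 27 or 30 per arm.

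**Assumed.** The pre/post correlation r of DASS-21 is not given. I use 0.5 to 0.7 as the main range and show 0.3 and 0.8 as well. Pre and post SDs are taken as equal.

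**The plan's own figures.** Effect size 4/8 = 0.5 and attrition 54/0.9 = 60 both reproduce. The 54 does not follow from the stated inputs: at 80% power, two-sided, a paired t-test needs 34 and a two-arm t-test needs 64 per arm. That is a separate problem. It matters here only because it sets the starting power.

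**Baseline tests.** Suppose a binary factor splits 18/30 v 12/30, that is 60% v 40%. The pooled proportion is 0.5, so every expected count is 15 and uncorrected χ² = 4 × (3²/15) = 2.4, p = 0.12. At 27 per arm, 16 v 11 gives p = 0.17. Around 50%, the smallest gap that reaches p < 0.05 is 19 v 11 of 30 (27 points) or 17 v 9 of 27 (30 points). A 20-point gap therefore passes as non-significant.

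**Shift left in a change-score contrast.** With equal SDs, SD of differences = SD × √(2(1 − r)), so SD = 8/√(2(1 − r)). If the arms differ at baseline by 0.4 SD, the change-score contrast differs from the baseline-adjusted one by 0.4 × (1 − r) × SD:

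- r = 0.5: SD = 8.00; shift = 0.4 × 0.5 × 8.00 = 1.6 points
- r = 0.7: SD = 10.33; shift = 0.4 × 0.3 × 10.33 = 1.2 points

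That is 40% and 31% of the 4-point target. The shift favours whichever arm starts with the worse score.

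**Precision.** The ANCOVA residual variance is SD²(1 − r²). Dividing by the change-score variance 2·SD²(1 − r) gives (1 + r)/2, so the residual SD is 8 × √((1 + r)/2). Power is for a two-sided two-sample t-test of 4 points at 27 per arm.

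| Analysis | Variance relative to change score | Residual SD | Power |
|---|---|---|---|
| Change score | 1.00 | 8.00 | 44% |
| ANCOVA, r = 0.3 | 0.65 | 6.45 | 61% |
| ANCOVA, r = 0.5 | 0.75 | 6.93 | 55% |
| ANCOVA, r = 0.7 | 0.85 | 7.38 | 50% |
| ANCOVA, r = 0.8 | 0.90 | 7.59 | 48% |

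The degree of freedom spent on the covariate changes none of these power figures at the precision shown.

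**The case against.** The strongest reply is that the article condenses a fuller plan, that covariate choice is commonly left to that plan, and that the larger defect is the absence of any between-arm outcome test. The last part is right: which covariates to use only becomes a question once a between-arm model exists. But section 2.5 is not silent. It names the outcome test, and that test excludes both an arm term and a covariate.

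Several stronger readings go beyond the document:

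- **That the χ² tests are a balance check on which decisions rest.** The text gives no purpose for them, and nothing is said to depend on their result. Comparing the randomised arms is the natural reading, but it is inferred.
- **That the χ² approximation will fail for dementia type.** Section 2.3.1 does say "There is no restriction on the type of YOD", but χ² is offered only as an example, so an exact test would fit the wording, and no distribution of types is given.
- **That baseline is ignored.** Paired t-tests use the starting score by differencing. The loss is relative to ANCOVA.
- **That an unflagged imbalance could move the result by up to about 3 points.** That figure comes from comparing unadjusted post scores, where the shift is 0.4 × r × SD (0.4 × 0.7 × 10.33 = 2.9). The plan works with pre/post differences, for which the range is 1.2 to 1.6 points.
- **That many baseline tests will raise false alarms.** Section 2.5 names two factors as examples; any larger count is a guess.
- **That MMSE should be adjusted for in the primary analysis.** Nothing in the document links MMSE of the person with YOD to caregiver DASS-21.

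**Conclusion.** The point holds in a limited form. Dropping the baseline p-values is mainly a matter of reporting. The part that changes results is replacing the unadjusted paired t-tests with a between-arm model that adjusts for the baseline score.

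The gain is moderate: 15% to 25% less variance than a change-score comparison, 6 to 11 percentage points of power at 27 per arm, and removal of a shift of roughly 1.2 to 1.6 points should a 0.4 SD imbalance occur. All three rest on an assumed pre/post correlation of 0.5 to 0.7, equal pre and post SDs, and the plan's SD of differences of 8. The 0.4 SD imbalance is an illustration, not a prediction.

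A reader might infer that adjustment rescues the sample size. It does not: at these correlations power at 27 per arm is 50% to 55%, against a stated 80%.

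**What to change.** In section 2.5, replace the paired t-tests with a between-arm ANCOVA for each outcome: post-program score on arm, adjusted for the baseline score of that same outcome. State in advance that this covariate is used whatever the baseline table shows. Baseline MMSE may be added for outcomes of the person with YOD, if that is also fixed in advance. Show baseline characteristics by arm as descriptive statistics only, and delete the between-group significance tests on them.

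The cost is plan wording and one degree of freedom per covariate. The data are already to be collected, and the data availability statement says the trial has not commenced, so the model can be fixed before any data are seen. The sample size needs its own correction.

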As far as we are aware, there have been no published interventions that focus on the dyad in YOD. Given the need to design psychosocial interventions that address the dyad as a unit, are accessible for busy caregivers, and are engaging and calming for people living with YOD, a combined music therapy and psychotherapy program delivered online, Music And Psychology & Social Connections (MAPS) was designed and will be tested using a pragmatic, wait-list control trial design. The present study aims to improve the mental health and social connectedness in caregivers and people with YOD, improve coping skills in caregivers, and decrease neuropsychiatric symptoms in people with YOD. The primary hypothesis is that the MAPS program will have a larger effect on improving depressive, anxiety, and stress symptoms in caregivers compared with standard care. Secondarily, we hypothesise that compared with standard care, MAPS will lead to greater improvements in: (a) depressive symptoms in people living with YOD; (b) the effectiveness and types of coping strategies utilised by caregivers; (c) levels of social connectedness in people living with YOD and their caregivers; and (d) the levels of neuropsychiatric symptoms in the people living with YOD.

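### The only test stated for the outcomes is a paired pre/post t-test, which gives no MAPS-versus-waitlist comparison, so the superiority hypothesis is not tested as written

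*Protocol article*

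**What the plan says.** The objective is a comparison between arms. The Introduction's primary hypothesis is that "the MAPS program will have a larger effect on improving depressive, anxiety, and stress symptoms in caregivers compared with standard care". Section 2.1 has dyads "randomised to one of two conditions: (1) MAPS; or (2) Waitlist control", says that the design "will test the primary and secondary hypotheses with a 1:1 allocation ratio", and adds that "we hypothesise that the MAPS group will be superior to usual care for the primary outcome measure".

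The analysis is specified in section 2.5, whose heading includes the statistical analysis plan. For outcomes it says: "Paired *t*-tests will be used to compare pre- and post- primary and secondary outcomes". The effect sizes promised in the same sentence describe the size of the changes. The one comparison of groups in that section is a χ² test on characteristics such as dementia type and gender. No section names a between-arm test of any outcome.

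The sample size in section 2.5 has the same basis: a 4-point pre/post reduction with an SD of differences of 8, effect size 0.5, 80% power and α = 0.05, giving 54 dyads, or 60 after 10% attrition.

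**The concern.** A paired t-test asks whether the mean change in one set of people differs from zero. Run within each arm, it gives two separate answers and no contrast between them; a significant change in one arm and a non-significant change in the other is not evidence that the arms differ. Run on all dyads together, it does not use the allocation at all.

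What is at stake is the purpose of the waitlist. It is there to show what happens over eight weeks without MAPS. If the outcome test does not use it, then easing of distress over time, the effect of being studied, or any other change shared by both arms can be credited to the program.

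**Working it through.** **1. The plan's own figure.** Inputs from section 2.5: reduction 4, SD of differences 8, so d = 4/8 = 0.5; power 80%; α = 0.05; sidedness not stated.
- Paired t-test, two-sided, 80% power: n = 33.4, so 34.
- Paired t-test, one-sided, 80% power: n = 26.1, so 27.
- Two-sample t-test, two-sided, 80% power: 63.8 per arm, so 64 per arm and 128 in total.
- Two-sample t-test, one-sided, 80% power: 50.2 per arm, so 51 per arm and 102 in total.

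None of these is 54. Two routes do reach it: a two-sided paired test at 95% power (n = 53.9), or twice the one-sided paired n of 27. Both are within-person calculations, which suggests that the paired sentence is not a slip confined to the analysis paragraph. The attrition step reproduces: 54/0.9 = 60.

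**2. What a paired test does when MAPS has no effect.** Take 54/2 = 27 analysed dyads per arm and an SD of change of 8, and let both arms improve by the same amount c. The paired t statistic has 26 degrees of freedom and non-centrality c√27/8; the two-sided 5% critical value is 2.056. Let p be the probability that one arm's test is significant. The arms are independent, so significance in MAPS but not in the waitlist has probability p(1 − p), counting only significance in the direction of improvement for MAPS.

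| Shared improvement c | Non-centrality | p (MAPS arm significant) | MAPS significant, waitlist not |
|---|---|---|---|
| 0 | 0 | 5% (2.5% towards improvement) | 2% |
| 1 | 0.65 | 10% | 8% |
| 2 | 1.30 | 24% | 18% |
| 3.1 | 2.01 | 49% | 25% |
| 4 | 2.60 | 71% | 21% |
| 5 | 3.25 | 88% | 11% |

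The values of c are illustrative; the document gives none. The last column cannot exceed 25%, because p(1 − p) peaks at p = 0.5, and c = 3.1 is about where that occurs.

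A single paired test on all 54 dyads would be significant 44% of the time at c = 2 and 95% at c = 4.

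**3. What a between-arm analysis would deliver at the planned size.** Assume that 4 points is the difference between arms and 8 the SD of change in each arm. The document gives both only for pre/post change.
- Change scores: d = 4/8 = 0.5; with 27 per arm, two-sided 5%, power is 44%. The difference detectable with 80% power is 0.777 × 8 = 6.2 points.
- ANCOVA: with pre/post correlation ρ and equal variances, residual SD = 8√((1 + ρ)/2). At ρ = 0.5 (assumed; none is given) this is 8√0.75 = 6.93, so d = 4/6.93 = 0.577 and power is 55%.
- Range for ANCOVA: 61% at ρ = 0.3 (residual SD 6.45) and 50% at ρ = 0.7 (residual SD 7.38).

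**The case against.** The strongest reply is that the article is condensed. Section 2.5 gives a short list of tests, does not label the paired t-test as the primary analysis, and does not exclude others. A fuller analysis plan may exist, and masking the post-program assessors to allocation makes most sense if the arms are to be compared. This limits the point: a reader might infer that the investigators have decided to ignore the waitlist, and the document does not show that. It does not remove the point. The article does not leave the outcome test open; it states one for the primary and secondary outcomes, and that test cannot address the hypothesis in the Introduction and section 2.1.

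A reader might also argue from regression to the mean, because caregivers qualify by a high score, for example if they "score either ≥14 on the Depression subscale of the Depression Anxiety and Stress Scale". That would need the screening score to serve as the baseline. Section 2.5 points the other way: dyads who have passed screening are invited to a session where the pre-program measures are completed. No figure here rests on regression to the mean.

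Finally, a reader might quote 25% as the plan's false-positive rate. It is the mathematical ceiling of one decision rule (significant in MAPS, not in the waitlist) that the document does not state, and it applies only near one value of the shared change. The size and even the direction of any shared change are unknown; with a progressive disease, untreated caregiver distress could worsen. The defect itself does not depend on any of this: with no shared change at all, the superiority hypothesis is still untested.

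**Conclusion.** The point stands, as a stated rule that does not fit the hypothesis rather than a missing detail. The trial claims superiority over usual care, and the only outcome test given contains no treatment contrast. This must be corrected before analysis.

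The size is best given as a range. With no MAPS effect, 27 per arm and an SD of change of 8, the MAPS-arm paired test is significant about 10% to 71% of the time for shared improvements of 1 to 4 points, and MAPS significant with the waitlist not about 8% to 25% of the time. The conclusion that the hypothesis is untested rests on the text alone. The percentages rest on the plan's SD, equal arms and the illustrative shared changes.

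**What to change.** Replace the paired t-test sentence in section 2.5 with wording such as: *The primary analysis compares the arms on post-program caregiver DASS-21 by ANCOVA, with randomised arm as the factor and baseline DASS-21 as covariate, all dyads analysed as randomised. The treatment effect is the adjusted between-arm difference with its 95% confidence interval. Continuous secondary outcomes use the same model. Within-arm changes are descriptive only.* The sentence should name the DASS-21 score to which it applies.

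Restate the power for that contrast at the planned size, without enrolling more: with 27 analysed per arm, a 4-point arm difference and an SD of change of 8, about 44% on change scores and about 55% by ANCOVA at a pre/post correlation of 0.5, with a detectable difference of about 6.2 points at 80% power on change scores. Give these as assumptions.

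The analysis itself needs no new data: baseline and week-8 measures are already planned, and the named software fits the model. According to the Data Availability statement the trial had not commenced, so the change can be made in advance. The cost is a less favourable stated power than the present 80%.
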